### Statistical analysis

The incremental areas under the curve (iAUC) will be calculated by using the trapezoidal rule (37) for PGR. All areas below pre-prandial glucose are excluded from the calculations. Two-factor repeated-measures analysis of variance (ANOVA) is performed to analyze the effects of treatment × time on outcome variables measured over the crossover study period, including iAUC for PGR and post-prandial glucose excursion. When treatment and time interaction are statistically significant, one-factor ANOVA and Bonferroni's *post-hoc* tests for multiple comparisons are performed to investigate the effect of treatment on the aforementioned measurement of PGR. Comparison between baseline and end-points is assessed by paired Student's *t*-test. Values are presented as mean ± SEM unless otherwise indicated. *P*-values of <0.05 are considered statistically significant. All analyses are performed with SPSS software version 25 (SPSS Inc., Chicago, IL, USA).

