### First week

Participants consumed the same test meals for 4 consecutive days according to a randomized crossover order: (1) Fitmeal pre-load 30 min before standard lunch meal (P + L), (2) Fitmeal as mid-meal snack 2 h before standard lunch meal (S + L), (3) co-ingestion of Fitmeal with standard lunch meal (CL) at the same time, containing 46.2 g of available carbohydrates where the Fitmeal contributes 8.1 g and standard meal provides 36.1 g, and (4) drinking water 30 min before standard lunch meal (W + L). To control the impact of different types of breakfast on the glycemic response of the next meal, the same breakfast will be provided to all participants on 4 test days. Participants are instructed to start breakfast, mid-meal snack, pre-load, and lunch at 8:00 a.m., 10:00 a.m., 11:30 a.m., and 12:00 p.m., respectively, during test days. Participants will be suggested to consume biscuits for 5 min and test meals for 10–15 min with 200 ml of water. During each test day, participants are required to have a 12-h fast, without strenuous exercise performed, and without alcohol consumed during the past 24 h before the breakfast meals. Extra foods and beverages are not permitted to consume from the time of starting breakfast to 3 h post-lunch during each test day, with specific reasons and benefits informed by the research nurse. In the event that participants consume extra food during the test period, they are required to record in the paper logbook to monitor compliance and report to the research nurse in time. Even if not reported, abnormal glucose excursions monitored by CGM will also provide objective information to the research team for evaluation.

Participants will wear CGM (FreeStyle Libre 1, FSL1, Abbott Diabetes Care, Inc., Alameda, CA) that measures interstitial glucose concentrations for the first week. On days 1 and 2 of CGM use, women are instructed to eat at their diet routine for monitoring baseline glucose profile. On days 3–6, women are instructed and reminded by the research nurse to consume the test foods provided according to their randomized order. On day 7, the CGM will be removed, and data from days 3 to 6 will be extracted for comparison of different test meals. From day 1 to 6, participants are required to record their food diary and the time to start each meal using the paper logbook, additional photos of each meal should be taken for a clear memory at later counseling.

### Counseling and 4 weeks of follow-up from week 2 to 5

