### Sample size

The sample size of the trial is estimated using PASS 15 Power Analysis and Sample Size software (NCSS, Kaysville, UT, United States). Assuming that the standard deviation (SD) is 32.9 mmol·min/L, a sample size of *n* = 39 provides 90% power to detect a change of 20 mmol·min/L in iAUC (*p* < 0.05) with Bonferroni correction, based on the previous study (36). Anticipating a 20% dropout rate, 49 subjects should be enrolled to obtain a final sample size of 39. Considering participants enrolled in four hospitals, 52 subjects will be enrolled with 13 subjects for each center.

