This proposed trial has some limitations. First, the free-living conditions of participants may raise non-compliance and bias as composed with in-site tests, although standard main meals for breakfast and lunch will be provided to participants to test acute PGRs by CGM. We will pre-set the automatic messages through WeChat Mini-Program to remind participants complying with each test meal, and the time to start each test meal will be confirmed in time by trained nurse. Second, CGM will be applied only two times at the baseline and after intervention rather than the whole period of intervention. It may not be possible to analyze the comprehensive glucose profile changes during the intervention, but a finger-prick blood glucose monitor will be provided to take daily blood glucose tests as a recommended regimen. Third, there is no washout period in-between 2 test days to minimize any carryover effects, but the same standard breakfast is provided to each participant to diminish the impact. Finally, the second stage of intervention is pragmatic and tailored based on optimal results from the first stage, it is impossible to implement randomization or to blind participants and investigators to provide robust evidence for confirming which dietary approach is better in improving post-prandial glycemic excursions with a 4-week intervention.

To minimize potential bias due to the study limitations, this study uses several approaches to reduce potential bias. First, to reduce the in-between differences in research sites, four tertiary hospitals in Chengdu city are selected for recruiting participants. Healthcare professionals and nurses working in the research sites are recruited to take training provided by the research team. Second, to improve data collection quality and reduce information bias, all electronic questionnaires in the proposed trial will be collected in a face-to-face interview by trained research assistants who are blinded to the treatment order and group assignments. All samples for laboratory tests are collected for centralized testing. Third, the study biostatistician, involved in data handling and analysis, will be blinded to participant study treatment and any potential identifiers.

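### The repeated-measures ANOVA named for the primary iAUC comparison by default drops all of a woman's lunches if one of the four is missing; a mixed model would keep them

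*Protocol article*

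**What the plan says.** All references are to the protocol article.

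- **Statistical analysis.** The method for iAUC and post-prandial excursion is stated as "Two-factor repeated-measures analysis of variance (ANOVA) is performed to analyze the effects of treatment × time on outcome variables measured over the crossover study period". If the interaction is significant, one-factor ANOVA with Bonferroni post-hoc tests follows. The software is fixed: "All analyses are performed with SPSS software version 25". Neither an SPSS procedure nor a mixed model is named.
- **First week.** The four meal plans take up four consecutive days: "On days 3–6, women are instructed and reminded by the research nurse to consume the test foods provided according to their randomized order". The sensor then comes off: "On day 7, the CGM will be removed, and data from days 3 to 6 will be extracted for comparison of different test meals". If a woman eats something extra, "they are required to record in the paper logbook to monitor compliance and report to the research nurse in time".
- **Sample size.** The allowance for loss is counted in women: "Anticipating a 20% dropout rate, 49 subjects should be enrolled to obtain a final sample size of 39". This is rounded up to 52, 13 at each of four hospitals.
- **Discussion (limitations).** The authors accept that "the free-living conditions of participants may raise non-compliance and bias". As a safeguard they send reminders, and "the time to start each test meal will be confirmed in time by trained nurse".

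**The concern.** A classical repeated-measures ANOVA with meal plan as the within-woman factor needs every cell filled. In SPSS the standard repeated-measures procedure deletes a woman listwise if one of her four iAUC values is absent, although the other three lunches still inform the contrasts between those meal plans.

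The design makes an occasional lost lunch plausible: test meals are eaten at home on four consecutive days, under fasting, timing and no-extra-food rules. It also makes the loss permanent, because days 3 to 6 are all used and the sensor is removed on day 7. The absence of a spare day does not cause the deletion; it only means the lunch cannot be recovered, so the choice of analysis decides how much else goes with it.

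At stake are precision in the primary comparison, the balance of the Latin square, and a sample-size margin that was set for whole-woman dropout but would also have to cover single lost lunches.

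**Working it through.** **Inputs from the Sample size section:** SD 32.9 and difference 20 mmol·min/L, 90% power, n = 39, 20% dropout, 52 enrolled. **Assumed, because the article does not give them:** loss rate p per lunch (q = 1 − p), losses independent across days, within-woman correlation 0.5.

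**1. The plan's own figures.** Treat 32.9 as the SD of a within-woman difference and use two-sided tests: n = ((z₁₋α/₂ + z₀.₉₀) × 32.9/20)².
- α = 0.05/4 gives 38.65, so 39.
- α = 0.05/3 gives 36.56, so 37 (40 with the t distribution).

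The stated 39 is reproduced as a paired calculation. A two-sample formula gives at least 57 per arm, so a within-woman analysis is what was planned. Dropout: 39/0.8 = 48.75, so 49; 4 × 13 = 52.

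**2. Women with all four lunches:** 52 × q⁴.
- p = 5%: 52 × 0.8145 = 42.4
- p = 10%: 52 × 0.6561 = 34.1

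**3. Loss the margin can absorb before falling below 39 complete women.**
- No other dropout: 1 − (39/52)^(1/4) = 6.9% per lunch.
- With 20% of women lost outright, 52 × 0.8 = 41.6 remain: 1 − (39/41.6)^(1/4) = 1.6% per lunch.

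**4. Effective number if all available lunches are used.** With correlation 0.5, a woman with k lunches has inverse covariance proportional to I − J/(k+1), where J is the matrix of ones. Averaging over missingness patterns, the information on a two-meal contrast, relative to a complete woman, is

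e(q) = q × (1 − E[1/(2+B₃)]) + q² × E[1/(3+B₂)], with B₃ ~ Bin(3, q) and B₂ ~ Bin(2, q).

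- q = 0.95: 0.95 × (1 − 0.20776) + 0.9025 × 0.20508 = 0.9377; × 52 = 48.8
- q = 0.90: 0.90 × (1 − 0.21605) + 0.81 × 0.21033 = 0.8759; × 52 = 45.5

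Variance ratio, complete-case to all-available: 0.9377/0.8145 = 1.15 and 0.8759/0.6561 = 1.34. For correlations from 0.3 to 0.8 the ratios stay at 1.15–1.16 and 1.33–1.34. A simulation of the plan's four sequences with period terms in the model gave effective numbers of 48.7 against 42.0 and 45.3 against 33.6, which is practically the same.

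**5. Power** (normal approximation, α = 0.05/3, period in the model, correlation 0.5). For reference, 39 complete women on this scale, ignoring period: 20 × √39/32.9 − 2.394 = 1.402, or about 92%.

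| Whole-woman dropout | Loss per lunch | Complete women | Power, complete women only | Power, all lunches |
|---|---|---|---|---|
| 0% | 5% | 42.4 | 93.9% | 96.8% |
| 0% | 10% | 34.3 | 87.0% | 95.5% |
| 20% | 5% | 33.9 | 86.6% | 91.5% |
| 20% | 10% | 27.2 | 76.4% | 89.3% |

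(The counts are simulated, hence 34.3 beside 34.1 in step 2.)

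**6. If losses cluster.** With 10% of lunches lost but all of them in the same women, 52 × 0.9 = 46.8 women are complete, not 34. The independence figures are therefore the unfavourable end of the range.

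**The case against.** The article states no complete-case rule. It names a method and a package, SPSS 25 can also fit mixed models, and missing-data handling may sit in an analysis plan that is not shown. The follow-up one-factor ANOVA is not even labelled as repeated measures. This stands to the extent that deletion is the default consequence of the named method, not a written rule. It does not remove the point: an analysis plan that follows the named method inherits the default, and a one-factor ANOVA run without pairing would give up the within-woman comparison on which the 39 rests.

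Several stronger readings are tempting, and the document does not support them.

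- *A lunch with extra food, or one not logged, is lost.* Extra food is recorded and reported, and unusual glucose excursions are passed to the team for evaluation, but no sentence excludes such a lunch. An unlogged lunch still has a scheduled noon start, a nurse's confirmation of the time, and sensor data. Only an iAUC that is really missing, or that the team sets aside, triggers deletion.
- *The trial will be underpowered.* At 5% independent loss and no other dropout, 42 women exceed the 39 required. A shortfall needs higher loss or added withdrawal, and no loss rate is given.
- *The complete-case result is biased whenever loss relates to response.* These are within-woman contrasts. With a common meal effect, loss related to a woman's overall glucose level cancels. Bias needs loss tied to meal-specific responses.

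**Conclusion.** The point holds as a conditional loss of efficiency that can be avoided. Followed as written, with the SPSS default, the primary iAUC analysis discards valid lunches from any woman who lacks one of the four, and the planned dropout allowance was not sized for that. Under independent loss the variance penalty is about 15% at 5% loss and 34% at 10%. It hardly depends on the assumed correlation, but it shrinks if losses cluster within women. Whether it matters for power depends on other dropout: the margin tolerates about 7% loss per lunch with none, and about 1.6% once the planned 20% is used up. A mixed model does not guarantee the planned power either: with 20% dropout and 10% lunch loss its effective number is 41.6 × 0.8759 = 36.4, against 41.6 × 0.6561 = 27.3 complete women. The loss rates, their independence and the correlation are assumptions. The change is worth making because the gain is real and the cost is small.

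**What to change.** For iAUC, replace the repeated-measures ANOVA with a linear mixed model (SPSS MIXED):

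- fixed effects for meal plan, period (test day) and sequence, and a random effect for woman;
- every valid test lunch included, with a short statement of when a lunch's iAUC counts as valid;
- Bonferroni-adjusted contrasts between meal plans;
- the all-four-lunches analysis kept as a sensitivity analysis;
- the number of valid lunches reported by meal plan and by sequence.

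The period term is needed: once partial sequences enter, meal plan and day are no longer balanced. A woman who stops after two test days contributes only days 3 and 4, and without the term a day effect would leak into the meal contrasts.

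The cost is a change of analysis wording in the software already named, with no change to visits, meals or sample size. The downside is that the model assumes lost lunches are missing at random given the lunches observed. Setting its results beside the sensitivity analysis and the lunch counts lets a reader see how much depends on the incomplete women, but does not test that assumption.

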A dietary strategy confirmed to be effective for reducing PGR individually is of paramount importance in increasing compliance with a recommended meal plan. Therefore, to optimize the use of low-GI biscuits in reducing individual PGR and provide valuable information in clinical practice of preventing T2DM for post-partum women with recent GDM, this proposed study will be conducted in two phases. The first phase (week 1) is designed with a randomized crossover trial with the main objective to compare the effect of low-GI biscuits consumed as pre-loads or as mid-meal snacks on individual PGR of the following main meal assessed by CGM. In the second phase (weeks 2–5), individualized intervention either with pre-loads or mid-meal snacks will be conducted depending on the results of personal PGR from the first phase. The objectives of the second phase are to observe before–after differences among all participants in their glycemic control using CGM metrics and glycated albumin (GA), dietary behavior, and psychosocial factors and compare those differences between the two dietary strategies. This article presents the development of the study design and procedure.

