## Methods

### Study design

This is a randomized, crossover, and a non-blinded trial comparing the effects of four different test meals over four consecutive days on PGRs in women with recent GDM. The four meal plans are as follows: (1) Fitmeal pre-load 30 min before standard lunch meal (P + L), (2) Fitmeal as mid-meal snack 2 h before standard lunch meal (S + L), (3) co-ingestion of Fitmeal with standard lunch meal (CL) as isocaloric standard control, and (4) 200 ml of water taken 30 min before standard lunch meal (W + L) as a placebo control. All participants will complete four test meals during the trial period in a randomized counterbalanced order by Latin Square Design (Figure 1). Crossover randomization process is performed by the study biostatistician. Different orders for four test meals will be concealed in envelopes. Each subject is randomized by dispensing the next sequentially numbered subject code and opening the corresponding code envelope indicating the order for four test meals.

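### The step that yields the primary meal contrasts is named as a plain one-factor ANOVA, without a repeated-measures or woman term, although the trial is a crossover sized on within-woman differences

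*Protocol article*

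**What the plan says.** All references are to the protocol article.

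- **Study design:** "All participants will complete four test meals during the trial period in a randomized counterbalanced order by Latin Square Design". Each woman therefore contributes four lunches, one per meal plan.
- **Introduction:** the randomised crossover of week 1 carries the main objective of comparing the biscuit strategies: "The first phase (week 1) is designed with a randomized crossover trial with the main objective to compare the effect of low-GI biscuits".
- **Primary outcome:** the 3-h post-lunch iAUC under the pre-load (P + L) and the snack (S + L) is compared with the co-ingestion control (CL) and the water control (W + L).
- **Sample size:** "Assuming that the standard deviation (SD) is 32.9 mmol·min/L", and n = "39 provides 90% power to detect a change of 20 mmol·min/L in iAUC", "with Bonferroni correction, based on the previous study (36"). The section does not say whether 32.9 is the SD of one meal or of a within-woman difference. It gives no correlation and no number of comparisons.
- **Statistical analysis:** the first step is a two-factor repeated-measures ANOVA of treatment by time. The second step reads "When treatment and time interaction are statistically significant, one-factor ANOVA and Bonferroni's" post-hoc tests, and this is the step that examines the treatment effect. The baseline-to-end-point comparison in the same paragraph is a paired t-test.

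**The concern.** The paragraph marks dependence in two places: repeated measures for the first step, paired for the before-after test. The step between them, which delivers the primary meal contrasts, has no such mark. Taken literally, a one-factor ANOVA with Bonferroni post-hoc tests is the procedure for four separate groups of women.

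Run on crossover data, that procedure leaves the four meal means and their differences unchanged but gives them the wrong standard error. The pooled error contains the stable differences between women that the crossover is meant to remove. With positive within-woman correlation the confidence intervals are too wide, the test falls below its nominal error rate, and real meal differences are missed more often than the Sample size section implies. This holds even if there are no period or carryover effects, so it is separate from how those are handled.

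**Working it through.** **Inputs.** From Sample size: SD 32.9, difference 20, n = 39, power 90%, Bonferroni. From Statistical analysis: significance level 0.05 ("values of <0.05 are considered statistically significant"). Assumed, because not stated: two-sided testing; k = 3, 4 or 6 comparisons; within-woman correlation rho from 0 to 0.7, equal for all meal pairs. Of the values of k, 4 is P + L and S + L each against CL and W + L, 6 is all pairs, and 3 is a lower bound.

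**Step 1. Reproduce n = 39.** Paired formula with 32.9 as the SD of the difference:

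n = ((z₁₋₀.₀₂₅/ₖ + 1.282) × 32.9/20)²

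| k | z | n, normal formula | power at n = 39, paired t (38 df) |
|---|---|---|---|
| 3 | 2.394 | 36.6 → 37 | 89.6% |
| 4 | 2.498 | 38.6 → 39 | 87.3% |
| 6 | 2.638 | 41.6 → 42 | 83.7% |

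The stated 39 is matched exactly by k = 4 with the normal formula, and nearly by k = 3 with the t distribution. Independent groups with SD 32.9 would need 74, 78 or 84 values per meal, and 57 even with no Bonferroni correction. The sizing is therefore a within-woman one. Reading 32.9 as the per-meal SD with rho 0.5 is the same calculation, since the SD of the difference is then 32.9 × √(2 × 0.5) = 32.9.

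**Step 2. What a between-groups ANOVA does to the standard error.** Let σ be the per-meal SD.

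- True variance of a meal difference: 2σ²(1 − rho)/n.
- Variance that the between-groups ANOVA uses: 2σ²/n.
- Overstatement: 1/(1 − rho), which is 1 at rho 0, 1.43 at 0.3, 2 at 0.5 and 3.33 at 0.7.

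Holding the SD of the difference at 32.9, σ = 32.9/√(2(1 − rho)), which is 23.3, 27.8, 32.9 and 42.5. The true standard error is 32.9/√39 = 5.27 throughout.

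Hand check at rho 0.5, k = 4:
- The between-groups standard error is 32.9 × √(2/39) = 7.45.
- The critical t (152 df) is 2.528, so the observed difference must exceed 2.528 × 7.45 = 18.8.
- Power is about Φ((20 − 18.8)/5.27) = Φ(0.22) ≈ 59%.

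**Step 3. Power of the contrast by simulation.** Correlated data, n = 39, four meals, difference 20, at least 20,000 trials per case:

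| rho | between-groups, k = 3/4/6 | repeated-measures contrast (114 df), k = 3/4/6 |
|---|---|---|
| 0 | 91/90/87% | 91/89/86% |
| 0.3 | 81/78/73% | 91/89/86% |
| 0.5 | 65/59/51% | 91/89/86% |
| 0.7 | 29/23/16% | 91/89/86% |

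A non-central t calculation for truly independent samples is not adequate here. It ignores that the observed difference varies less than the test assumes, and it gives 37% rather than 29% at rho 0.7, k = 3.

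**Step 4. If 32.9 is the per-meal SD instead.** For k = 3, between-groups power rises from 60% at rho 0 to 68% at rho 0.7. For k = 6 it stays near 51%. The repeated-measures contrast has 78/70% (k = 3/6) at rho 0.3, 91/86% at 0.5 and 99/99% at 0.7. The between-groups test is again the weaker one at each of these positive correlations.

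**Step 5. Error rate.** With no meal effect and rho 0.5, the between-groups omnibus F rejects in about 0.3% of trials or fewer, against a nominal 5%.

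**The case against.** The strongest reply is that the authors probably mean a one-factor repeated-measures ANOVA. The preceding sentence says repeated measures, the next steps from two factors to one for the same measurements, the design is within-subject throughout, and the before-after test is paired. A journal article also condenses, and a modifier may simply not have been repeated. All of this stands: under that reading there is no loss from this source. It does not settle the matter, because the article does name a test for the primary contrasts, and an analyst following the name could run the wrong one.

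A reader might infer that the plan treats the four lunches as independent and that power therefore falls from 90% to some fixed figure near 50-65%. The documents support neither. They nowhere state independence, and any single power figure needs a correlation and a number of comparisons that they do not give. At correlation 0 there is no loss at all.

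Two further points stand. The error would be conservative: estimates are unaffected and false positives become rarer. And the contrasts are reached only after a significant treatment-by-time interaction. The figures here ignore that gate, so they are not the power of the whole procedure.

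**Conclusion.** The point holds as a conditional one. The named follow-up test does not match the crossover or the sizing and, if run literally, makes the 90% power statement inapplicable whenever a woman's four responses are positively correlated. Positive correlation is the natural expectation, since the article itself stresses that women differ in their response to the same food. The size of the loss depends on unstated quantities. With 32.9 as the SD of the difference, it ranges from none at correlation 0 to severe at 0.7, and at an assumed 0.5 power is roughly 51-65% over 3 to 6 comparisons. Whether any loss occurs depends on which ANOVA is meant, which the text leaves open. It should be corrected before analysis because it concerns the primary outcome.

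**What to change.** In Statistical analysis, replace the plain one-factor ANOVA and its post-hoc tests with a one-factor repeated-measures ANOVA, or a mixed model with a random intercept for woman. State that the Bonferroni-adjusted meal contrasts are taken from within-woman differences (adjusted estimated marginal means or paired tests). In Sample size, it would help to add whether 32.9 is a per-meal SD or the SD of a difference, and how many comparisons the Bonferroni correction covers.

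The cost is one phrase of analysis wording, plus a clause in Sample size. The data are unchanged, the same software can be used, and no participants are added.

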**Figure 1 F1:**
[figure not shown]
Randomized crossover design. Participants will complete four test meals over 4 consecutive days in a randomized counterbalanced order using Latin Square Design. Participants will be randomized to receive one of the four meal arrangement orders as follows: (1) P + L → S + L → W + L → CL; (2) S + L → CL → P + L → W + L; (3) CL → W + L → S + L → P + L; (4) W + L → P + L → CL → S + L. To diminish the glycemic impact from the last meal, breakfast, lunch, pre-load, and mid-meal snack foods are provided, with breakfast and lunch identical for 4 test days. 3h-iAUC after each lunch using continuous glucose monitoring (CGM) will be calculated as the primary outcome (P, Pre-load; S, Mid-meal snack; B, Breakfast; L, Lunch; W, Water; C, Co-ingestion; iAUC, Incremental areas under the curve of post-prandial glycemic response; P + L, Fitmeal pre-load 30 min before lunch; S + L, Fitmeal as mid-meal snack 2 h before lunch; CL, Co-ingestion of Fitmeal with lunch; W + L, Drinking water 30 min before lunch).

Moreover, a before–after intervention of 4-week duration based on within-subject meal test results will be followed for all participants to compare changes in PGRs from the baseline. The study will be carried out at four maternal and child healthcare hospitals in Chengdu. The protocol (CWCCH 2021027) has been approved by the ethics committee of Chengdu Women's and Children's Central Hospital, and written informed consent has been obtained from all participants. The study is conducted in accordance with the principles expressed in the Declaration of Helsinki.

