**Physical measures**										
Weight and BMI	X							X	X	X
Height	X									
Waist circumference	X									X
Body fat %	X									

Glycemic metrics will be calculated with values from CGM and SMBG. Participants who have signed the consent form will wear the CGM (FreeStyle Libre 1, FSL1, Abbott Diabetes Care, Inc., Alameda, CA) two times, monitoring for 7 days on week 1 and 3 days on week 6, respectively. The FSL1 is the most used biosensor for intermittent scanned CGM. All glucose data will be given each 15 min with a total of 96 readings every 24 h. From all these glucose measurements, several glucose metrics are calculated and reported on a 24-h basis average, including the percentage of time in a range from 3.9 to 10 mmol/L (TIR), percentage of time above range (TAR), percentage of time below range (TBR), a standard difference of mean glucose (SD), mean amplitude of glycemic excursions (MAGE), %CV, average glucose concentration (AG), incremental areas under the curve (iAUC), and post-prandial glycemic excursions (PE). Changes in glycemic metrics are calculated by subtracting the averaged values obtained on day 1 and 2 with CGM use at the baseline from the averaged values obtained on the second and third days of CGM use at the end-point. iAUCs will be calculated to represent the PGRs of four test meals from day 3 to 6, respectively. SMBG will be tested by glucose meter data (Qin Zhi, Sinocare, Inc., Changsha, China) six times a day in a paired test regimen at pre-meal and 1 h post-meal, at least 2 days per week from week 2 to week 5. SMBG frequency, average fasting, and pre-meal blood glucose concentrations, average 1 h post-prandial glucose concentrations (1hPG), and 1 h post-prandial excursions (1hPE) will be calculated. CGM and glucose meter data (An Wen/Qin Zhi, Sinocare, Inc. Changsha, China) will be uploaded automatically to the data platform and will be analyzed at the end of each monitoring period.

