### Outcome

#### Primary outcome

The 3-h post-lunch incremental areas under the curve of post-prandial glycemic responses (iAUC) using CGM are compared between the low-GI biscuits as pre-load food (P + L) or mid-meal snack (S + L) and their isocaloric standard control of co-ingestion (CL) and placebo control (W + L) in women with recent GDM. Primary outcomes also include differences in CGM measures (AG, SD, %CV, MAGE, TIR, TAR, TBR, and PE) and GA after a 4-week intervention compared with those variables at the baseline.

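### The only stated route to the primary meal comparison on 3-h iAUC runs through a significant treatment × time interaction, although iAUC is a single value per woman per meal

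*Protocol article*

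**What the plan says.** The Statistical analysis section starts the crossover analysis from a two-factor model for repeated measures. In its words, "analysis of variance (ANOVA) is performed to analyze the effects of treatment × time on outcome variables measured over the crossover study period". It then names the variables that this model covers, and the primary one is among them: "including iAUC for PGR and post-prandial glucose excursion". The next sentence sets the follow-up. It begins "When treatment and time interaction are statistically significant, one-factor ANOVA", and adds that Bonferroni comparisons are then made to look at the meal effect. It does not say what happens to the meal comparison when the interaction is not significant, and it does not define time.

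Elsewhere the article treats iAUC as one value per test lunch. The Figure 1 legend says "3h-iAUC after each lunch using continuous glucose monitoring (CGM) will be calculated as the primary outcome", and the description of the glycemic metrics says "iAUCs will be calculated to represent the PGRs of four test meals from day 3 to 6, respectively". Under Primary outcome, the areas "are compared between the low-GI biscuits as pre-load food (P + L) or mid-meal snack (S + L) and their isocaloric standard control"; that control is the CL meal, and the water meal W+L is named as a second control. The design is a Latin square: "Participants will complete four test meals over 4 consecutive days in a randomized counterbalanced order using Latin Square Design". Under Sample size, the trial is sized for a Bonferroni-corrected change of 20 mmol·min/L in iAUC with 90% power.

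**The concern.** The primary question is whether mean iAUC differs between meals. That is a treatment main effect and a set of pairwise contrasts. An interaction asks something else: whether the meal effect varies over time. A meal strategy that works equally well on every test day has a main effect and no treatment × day interaction, so a rule that reaches the meal comparisons through the interaction blocks them in the very case the trial hopes to find.

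The rule also conflicts with the Sample size section, which computes power for a direct contrast with no preceding test. Followed literally with time as test day, the analysis would usually stop before the comparison for which the 39 evaluable women were planned.

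**Working it through.** **Inputs from the article.** SD 32.9 and change 20 mmol·min/L, 90% power, n=39 evaluable (Sample size); four printed meal orders, each meal eaten once per woman (Figure 1 legend); significance at 0.05 (Statistical analysis). **Assumptions.** Tests are two-sided. The article gives the SD as "Assuming that the standard deviation (SD) is 32.9 mmol·min/L" without saying whether it is per meal or of the within-subject difference; it is taken here as the latter.

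**1. What the planned sample size belongs to.** For a direct paired contrast with k Bonferroni comparisons, n = [32.9 × (z for 1 − 0.025/k + 1.282) / 20]².
- k=3: z = 2.394, n = 36.6.
- k=4: z = 2.498, n = 38.6, rounding up to 39.
- The exact t version gives 40 for k=3 (power 89.6% at n=39) and 42 for k=4.

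The article does not state k. Two strategies against two controls make 2 × 2 = 4 contrasts, and k=4 gives the stated 39 by the z formula. The 20% dropout step also reproduces: 39/0.8 = 48.75, so 49. The 90% power is therefore that of a direct meal contrast.

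**2. Time as test day.** Four meals by four days make 16 cells, and each woman supplies 4. A fully within-subject meal × day interaction cannot be formed. Across the four orders, the 16 order × day cells carry 15 df: 3 for order, 3 for day, 3 for meal and 6 left over. Those 6 df are the only available meal × day interaction. They would also absorb any carryover, so a significant result need not mean that the meal effect changes by day.

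**3. Chance of passing the precondition.** If the meal effect is constant and there is no carryover, the interaction null hypothesis is true. The test is then significant with probability 0.05, whatever the SD or n. Simulation agrees (5,000 trials, printed orders, residual SD 32.9/√2 = 23.3, model with participant, period and meal, then meal × period added):

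| True effect on iAUC | n | Interaction p<0.05 | Meal main effect p<0.05 |
|---|---|---|---|
| P+L and S+L both −20 | 39 | 5.6% | 99.7% |
| P+L only −20 | 39 | 5.3% | 97.5% |
| P+L and S+L both −20 | 52 | 5.5% | >99.9% |

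**4. Check of the main-effect column.** The noncentrality is λ = n × Σ(meal mean − grand mean)² / residual variance, with variance 32.9²/2 = 541.2 and 3 and 156 − 45 = 111 df at n=39.
- Both strategies −20: Σ = 4 × 10² = 400, λ = 39 × 400/541.2 = 28.8, power 99.7%.
- P+L only −20: Σ = 15² + 3 × 5² = 300, λ = 39 × 300/541.2 = 21.6, power 98.0%.

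The noncentral F and the simulation agree to within half a percentage point.

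**5. Time as the 15-min readings.** A 3-h window holds 180/15 + 1 = 13 readings per lunch. A treatment × time test on these is a test on glucose values. iAUC has already integrated over them, so no time factor remains for it. The test on the curves and the test on iAUC are different: two meals can differ in the shape of the curve and have equal areas.

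**The case against.** The strongest reply is that time most naturally means the post-lunch readings, especially since post-prandial excursion is listed alongside iAUC. Baseline-subtracted curves all start at zero, so a difference in mean area normally implies some treatment × time difference. Simulation on that reading bears this out (n=39, 13 readings, a 20 mmol·min/L reduction in P+L and S+L starting from zero, autocorrelated noise with correlation 0.5 to 0.9, Greenhouse-Geisser test). The interaction was significant in 99.8% to 100% of trials when the effect rose and faded, and in 60% to 66% when it was complete by 15 min and then flat. This stands: a 5% pass rate cannot be claimed for the curve reading. Nor can it be obtained there by imagining a constant upward or downward shift of the whole curve. Such a shift also moves pre-prandial glucose, from which the area is measured, and so leaves iAUC unchanged.

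Second, the text says when, not only when, and the two-factor ANOVA would print an omnibus meal effect. A reader might infer that the plan forbids the meal comparison without a significant interaction; it does not say so. But it gives the omnibus effect no role, and the pairwise contrasts named under Primary outcome appear only as the follow-up.

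Third, a standard repeated-measures procedure could not form the meal × day interaction fully within subject, so the 5% describes a sequence-group model that the article does not specify. That is correct, and is a further reason why the rule cannot be applied to iAUC as written.

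Fourth, an article leaves detail to an analysis plan. That would excuse silence on the definition of time, but not a stated decision rule that does not fit the primary outcome.

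**Conclusion.** The point holds as a wrongly stated decision rule for the primary crossover outcome. On neither reading of time is the interaction a suitable precondition for the meal contrasts on iAUC.

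The size depends on the reading. With time as test day and an effect constant across days, about 5% of trials would reach the meal contrasts, against about 98% to 99.7% detection by a direct meal test at n=39. The 5% does not depend on the SD or n; the 98% to 99.7% rests on 32.9 being the SD of the within-subject difference and on no carryover. With time as the 15-min readings, the precondition may often be met when a real effect exists, so the loss ranges from very small to roughly a third or more of trials in the shapes examined.

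A reader might infer that a real meal effect would normally go untested however the plan is read, or that the stated power and error rate are void. The documents do not support that: the first is true only for the day reading, no inflation of the error rate has been shown, and the Primary outcome and Sample size sections both point to an intended direct comparison.

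**What to change.** In the Statistical analysis section, remove the interaction precondition for iAUC. State instead that the meal effect on 3-h iAUC is tested directly in a crossover model with participant and period, followed by the Bonferroni-corrected contrasts of P+L and S+L against CL and W+L, whatever the result of any interaction test. Keep treatment × time only to describe the post-lunch glucose profile, with time defined there as the 15-min readings.

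This costs one sentence. It needs no new data and no change for participants or to the sample size calculation, which already assumes a direct contrast.
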